**Fig. 2 Fig2:**
[figure not shown]
Modified Child Dental Anxiety Scale Faces Version (Source: SDCEP Oral Health Assessment and Review 2017).^11^

**Fig. 3 Fig3:**
[figure not shown]
A child wearing the E4 wrist watch.

Throughout the second visit, the dental treatment for both study and control groups will include administering local anaesthesia and restoration of carious teeth, pulp treatment if needed and/or tooth/teeth extractions. The dental treatment will be carried out by the same paediatric dentist. However, a second paediatric dentist blinded to which group the child belongs to will record the FBRS of children while receiving the treatment under N_2_O sedation.

The MCDASf (see Fig. 2) using the SDCEP endorsed and condensed version of the MCDASf questionnaire,^11^ not including the last two questions on dental sedation and GA, will be used for all anxious children. The MCDASf is a validated tool that had been used to assess dental anxiety.^14–16^

The language of the MCDASf questionnaire will be English or Arabic. The English version was translated into Arabic using the forward and backward translation method. The translation was checked by an independent bilingual expert who resolved concerns and discrepancies. To make sure that the translation was effective, a back-translation to the English language was done by an independent translator who back-translated the questionnaire and discrepancies in the translation version were resolved. The total score range of MCDASf is 6–30. Children with a score ≥19 will be considered to have severe dental anxiety (dental phobia), while those with a score of <19 will be considered to have none to moderate anxiety (Table 2).^7^ The treatment complexity rank score (Table 3) records the medical status classification, based on the patient’s (ASA) classification.^13^

**Table 2 Tab2:** Modified Child Dental Anxiety Scores (MCDAS).

Score	Interpretation
5–10	Minimal anxiety
11–18	Moderate anxiety
≥19	Severe anxiety

**Table 3 Tab3:** Treatment complexity rank score.

Rank	Description	Score
Routine	Polishing, fluoride application, fissure sealants, one-surface Restorations	1
Intermediate	2-surface restorations, extraction of 1 primary tooth, one-quadrant restorative dentistry	2
Complex	Crown preparation, pulp treatment, extraction of multiple primary teeth, multiple-quadrant restorative dentistry, extraction of 1 permanent tooth	3
High complexity	Multiple extractions of permanent teeth, surgical extractions, biopsy. Any treatment considered more complex than above or are multiples of the above	4

In addition to the MCDASf, physiological anxiety-related changes will be recorded using E4^®^ wrist bands (see Fig. 3). The wrist band will be placed 5 min before the patient comes into the surgery for treatment and will be taken off 5 min after the completion of treatment. This will enable recording physiological parameters continuously before, during and after the dental treatment. E4^**®**^ wrist bands will provide real-time parameters (Fig. 4) such as EDA also known as GSR, BVP, acceleration, HR, and temperature. E4^**®**^ wrist bands are small, simulate wearing a wristwatch, and we do not anticipate any increase in the children’s anxiety as a result of wearing these wrist bands. The E4^**®**^ wrist band was validated^17^ and approved by the United States Food and Drug Administration as a medical device. It is used in a wide range of research settings with configurations for palmar skin conductance measurement or using gelled electrodes secured under the band. Additional evaluation of behaviour (Table 4) will be documented using the numerical FBRS scores (FBRS: 1–4, where 1 is very uncooperative).^12^ Parents and children will be asked to fill in the survey questionnaire after completion of dental treatment visit to assess their perception and approval (or lack of) of dental treatment with or without an accustoming session (Table 1a, b).

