### Inclusion and exclusion criteria

Inclusion criteria- Children (aged 5–15 years old) presenting with their parents, who are referred to the paediatric dentistry department in Dubai Dental Hospital (DDH) [the only secondary specialist dental hospital in Dubai, United Arab Emirates (UAE)], for dental treatment under N_2_O within a 6 months’ period will be invited to participate in the study.- Healthy children indicated for dental treatment under N_2_O with American Society of Anesthesiologists (ASA) classification of I or II.^13^- No learning disabilities impeding N_2_O sedation acceptance.UAE and non-UAE nationals’ parents and children will be eligible to participate in the study.- The children should have no previous experience of N_2_O inhalation sedation.Exclusion criteria- Medically compromised children and/or individuals with special healthcare needs.- Patients diagnosed with a psychiatric disorder.- Children who lack communication due to languages barriers.- Children whose parents refuse to participate in the study.- Patients with contraindications for the use of N_2_O, such as patients who have upper respiratory tract infections (common cold), mouth breathers due to nasal adenoids.- Patients with obvious skin conditions such as eczema or psoriasis that may impede the use of the E4^®^ wrist bands and impair their conductivity.

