**Fig. 1 Fig1:**
[figure not shown]
Flowchart of the study design.

A 1:1 allocation-based block randomisation method will be employed. The method of allocation concealment will be attained by using matching, sealed, serially numbered, non-transparent envelopes that will contain group allocation. The envelopes will be opened in sequence by a non-investigator (dental assistant), only after the envelope has been conclusively dispensed to each partaker and will continue to be anonymous to the clinical team.

At the initial screening visit, the anxiety level will be recorded using MCDASf (Fig. 2) to determine the need for N_2_O sedation and subsequently invite the child and parents to participate in the study. Once enroled, an acclimatising visit will be carried out by a single paediatric dentist who will not be involved in the subsequent treatment of the patients. To be constant, an information script will be organised and rehearsed so that the same preoperative instructions about N_2_O sedation will be delivered to all the children and their parents. The patient’s physiological signs will be recorded using the E4^®^ wrist band (Fig. 3). For the study group only, 15 min of N_2_O sedation will be administered without any dental treatment procedures at the acclimatisation visit.

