### The study’s statistical analysis

We will conduct deep statistical analysis after consideration of the data’s distribution normality, with the appropriate parametric or non-parametric statistical tests using the statistical software SPSS™ 24.0.0 (SPSS^©^ Inc., USA). The utilisation of standard descriptive statistics and quantitative data will be reported; if normally distributed, means and standard deviations shall be used; and if skewed, medians and interquartile ranges will be reported. The score of dental anxiety will be calculated for each participant and test for normality by using the Shapiro–Wilk test. Categorical data will be tested for independency by using Chi-square or Fisher's exact test when appropriate. The difference in the means between the two groups will be tested using either *t*-test or Mann–Whitney test depending on the normality of the data. The comparison of the means of more than two variables will be tested by using ANOVA or Kruskal–Wallis depending on the normality of the measurements. A *p*-value of <0.05 will be considered significant in all tests.

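### The treatment complexity score is described as ASA status in the text but as dental procedure difficulty in Table 3, and the article states neither its timing nor its role; fixed before allocation, it could serve as a covariate

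*Protocol article*

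**What the plan says.** Under Study flow and layout, the text introducing the table says: "The treatment complexity rank score (Table 3) records the medical status classification", and ties this to the patient's ASA class. Table 3 contains something else. Its lowest rank reads "Polishing, fluoride application, fissure sealants, one-surface Restorations" and its third rank reads "Crown preparation, pulp treatment, extraction of multiple primary teeth, multiple-quadrant restorative dentistry, extraction of 1 permanent tooth". The fourth covers multiple or surgical extractions and anything more complex.

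The Inclusion and exclusion criteria restrict entry to "American Society of Anesthesiologists (ASA) classification of I or II". Treatment at the second visit "will include administering local anaesthesia and restoration of carious teeth, pulp treatment if needed and/or tooth/teeth extractions".

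On allocation the article says "A 1:1 allocation-based block randomisation method will be employed" and names no stratification factor. In The study's statistical analysis: "The difference in the means between the two groups will be tested using either" a t-test or a Mann–Whitney test, according to normality. The complexity score does not appear among the primary or secondary outcomes, in the description of randomisation, or in the analysis section.

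**The concern.** There are two linked problems.

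The first is a contradiction over what the variable is. One sentence makes it a measure of general health; the table makes it a measure of how demanding the dental work is. If it were ASA, it would have two levels already narrowed by eligibility and would say nothing about the procedure.

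The second is that the score, read as Table 3 defines it, has no stated timing or purpose. FBRS is scored while the child is being treated, the wrist band records before, during and after treatment, and MCDASf is repeated afterwards. All of these are taken during or after procedures that differ between children, so it is plausible that difficulty accounts for some of their variation. A rank fixed before allocation could remove part of that variation from the comparison. A rank taken from what was done at the second visit could not safely do so: it is observed after randomisation and may itself depend on the arm, since a more cooperative child may receive more treatment.

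At stake are a recorded variable whose meaning is unclear and some precision in a trial with 33 children per arm.

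**Working it through.** **The definition, side by side**

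| Source | What the score would be | Levels possible in this trial |
|---|---|---|
| Sentence in Study flow and layout | ASA medical status | 2 (eligibility allows I or II) |
| Table 3 | Dental procedure difficulty | 4 (scores 1 to 4) |

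No reading makes the two agree.

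**The detectable difference behind 33 per arm**

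Inputs from Calculation of the study's sample size and The study's statistical analysis: 33 per group, 80% power, significance at 0.05. No effect size or SD is given, so the 33 cannot be reproduced forwards, only solved backwards. Two-sided testing is assumed because sidedness is not stated.

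- Normal approximation: d = (1.960 + 0.842) × √(2/33) = 2.802 × 0.246 = 0.69 SD.
- t-test: 0.70 SD.
- Mann–Whitney (relative efficiency 0.955): 0.71 SD.
- If the test were one-sided: 0.61 SD.

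**What adjustment would gain**

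If a covariate explains a share R² of outcome variance, the residual SD is multiplied by √(1 − R²), and the detectable difference shrinks by the same factor. The document gives no R², so these values are assumptions. The second column starts from the t-test value of 0.70. Power and n use the normal approximation at d = 0.69.

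| Assumed R² | Detectable difference (SD) | Power with 33 per arm | n per arm for 80% power |
|---|---|---|---|
| 0 | 0.70 | 80% | 33 |
| 0.05 | 0.70 × √0.95 = 0.68 | 82% | 32 |
| 0.10 | 0.70 × √0.90 = 0.66 | 84% | 30 |
| 0.20 | 0.70 × √0.80 = 0.63 | 88% | 27 |
| 0.30 | 0.70 × √0.70 = 0.59 | 92% | 24 |

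These figures ignore the few degrees of freedom that the covariates use.

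**Chance imbalance**

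Suppose half the children are at rank 3 or above (assumption). The difference in counts between arms of 33 then has SD √(2 × 33 × 0.25) = √16.5 = 4.06.

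- A gap of at least 15 percentage points needs 5 or more children: z = 4.5/4.06 = 1.11, probability about 27%.
- A gap of at least 20 points needs 7 or more: z = 6.5/4.06 = 1.60, probability about 11%.

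This is ordinary randomisation at this sample size. It shows how often the arms would look uneven on difficulty; it does not show bias.

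**The case against.** The strongest reply is that this is a drafting slip in one sentence. Table 3 is the scoring instrument, with explicit procedures and scores, and ASA class cannot sensibly be entered on it. A reader might infer that staff will record ASA and lose procedure difficulty. The document does not show that this will happen. The sentence still needs correcting.

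A reader might also infer that the trial leaves a major driver of behaviour uncontrolled. The document contains no figure linking procedure difficulty to FBRS, MCDASf or any E4 measure. Polishing, fluoride and sealants are not among the treatments listed for the second visit, so the range in practice may be narrower than Table 3 suggests. It is still not uniform: the listed work is "restoration of carious teeth, pulp treatment if needed and/or tooth/teeth extractions", and a one-surface restoration alone sits at rank 1 while multiple permanent extractions sit at rank 4. The link to outcome is plausible but unquantified.

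Nor can the score be called unused in the trial. That can be said only of this article, since a fuller protocol or analysis plan may give it a role, and silence about covariates in a condensed article is not a fault. What the article does state is a two-sample test that takes no covariate, and that statement can be improved.

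Finally, the unadjusted comparison is not biased. Chance imbalance is already allowed for in its type I error, so the 27% and 11% figures are not evidence of harm. The article also does not propose adjusting for treatment delivered; the caution about that applies to any later use of a score whose timing is undefined. Gains in SD units do not carry over directly to FBRS, which has four ordered levels.

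**Conclusion.** The contradiction is certain: the sentence and Table 3 define different variables, and the ASA limit confirms that the sentence does not describe the table. The article also leaves open whether the rank is planned or delivered, and gives it no role.

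On the analysis, the stated unadjusted comparison is valid, and adjustment would be a better method at little cost. The gain is modest: from about 0.70 SD to 0.66–0.63 SD, or from 80% to 84–88% power at the implied difference of 0.69 SD. It rests on three assumptions: two-sided testing, the back-solved detectable difference, and an R² of 10–20%. The sample size of 33 per arm does not depend on this point.

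**What to change.** 1. Correct the sentence so that the Table 3 score is procedure complexity, and record ASA class as a separate variable.
2. State when the rank is set: from the treatment plan at the initial examination, which already precedes randomisation, and before the envelope is opened.
3. Replace the unadjusted comparison of MCDASf with an ANCOVA of the post-treatment score on arm, baseline MCDASf (already collected) and planned rank.
4. Use the same covariates in a suitable model for each other measure: an ordinal model for FBRS and regression for the E4 measures.
5. Report treatment actually performed by arm, descriptively only, because it arises after randomisation.

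The cost is one corrected sentence, one entry at an existing visit, and regression in place of simple two-sample tests. A small drawback is that planned and performed treatment may differ for some children, which weakens the covariate without biasing the comparison. The rank should be fixed prospectively, because a clean pre-allocation value is hard to reconstruct afterwards.

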**Fig. 4 Fig4:**
[figure not shown]
The screenshot from the real-time physiological parameter interface obtained from the E4^®^ watch analytical software.

**Table 4 Tab4:** Frankl behaviour rating scale.^12^

	Frankl behavioural rating scale
Rank	Description
1 − −	Definitely negative: Refusal of treatment, forceful crying, fearfulness or any other overt evidence of extreme negativism.
2 −	Negative: Reluctance to accept treatment, uncooperative, some evidence of negative attitude but not pronounced (sullen, withdrawn).
3 +	Positive: Acceptance of treatment; cautious behaviour at times; willingness to comply with the dentist, at times with reservation, but patient follows the dentist’s directions cooperatively.
4 + +	Definitely positive: Good rapport with the dentist, interest in the dental procedures, laughter and enjoyment.

### Calculation of the study’s sample size

The study is sized to have an 80% power to detect a statistically significant difference in children’s behaviour and anxiety level between the two groups. As there are no previous similar studies, the primary outcome measure is a change in anxiety (a reduction mainly). To our knowledge, no studies had investigated the effect of an acclimatising session of N_2_O on the child’s behaviour to base our sample size calculation on. Our biostatistician used Houpt et al. study in 1996 (effects of nitrous oxide on diazepam sedation of young children) to predict the sample size.^18^ The predicted sample size is 33 participants in each group and to compensate for dropouts a total of 70 participants will be recruited for both groups.

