**Conclusions:**

This RCT will report whether prior acclimatising of a child to N_2_O sedation is effective, or not, in improving dental treatment behaviour.

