### Primary outcome

The changes in the child’s behaviour and anxiety levels. The primary outcome measures will be assessed byPhysiologically measurable parameters by using a medical grade wearable device (E4^®^ wrist bands—Empatica Inc., [name]—ISO 13485 Cert. No. 9124.EPTC*)*. These parameters areElectrodermal activity (EDA) also known as Galvanic skin response (GSR),Blood volume pulse (BVP),Heart rate (HR),Surface skin temperature.Dental anxiety scores at baseline before the (acclimatisation session) and after treatment (second session) using the Modified Child Dental Anxiety Scale-face version (MCDASf).^11^Children’s behaviour score will be recorded using the Frankl Behaviour Rating Scale (FBRS).^12^

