### Role of the participants and the general public in the study

*What was the research question, the outcome and outcome measures of the study and how were they developed?* A pilot questionnaire to explore the usefulness of an N_2_O acclimatising appointment prior to actual treatment, from the participants’ point of view was carried out in a group of 15 child participants (range: 5–15 years). The outcome of this survey was indecisive with 8 out of 15 children expressing a predilection for commencing treatment without an acclimatising session to N_2_O. This resulted in the formulation of the primary outcome measure of our study on investigating the differences in the participants reported dental anxiety scale in children belonging to the study and control groups.

*What were the preferences and experiences of the participants and their influence in designing the study?* We asked the aforementioned children regarding their feeling in carrying out the completion of the MCDASf (anxiety survey). All the children in this survey mentioned that completing MCDASf was acceptable to them. In addition, we showed and placed the E4 watch on their wrists and asked if they would be happy to wear the watch throughout the treatment. Out of 15 children, 13 were happy with wearing the E4 watch; 2 children found it uncomfortable.

*Involvement of participants in the recruitment to and conduct of the study*. The potential participants will already be patients indicated for N_2_O sedation and are on the DDH sedation list.

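### The 80% power is unsupported as stated: it is attached to two constructs, rests on a study of a different comparison, and for one measure 33 per arm corresponds to about 0.70 SD

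*Protocol article*

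**What the plan says.** All places are in the protocol article.

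- *Calculation of the study's sample size*: "The study is sized to have an 80% power to detect a statistically significant difference". The object of that power is a "difference in children’s behaviour and anxiety level between the two groups".
- The next sentence of that section says that "the primary outcome measure is a change in anxiety (a reduction mainly". It adds that no similar study exists, and that the biostatistician predicted the sample size from a study described as "effects of nitrous oxide on diazepam sedation of young children". The result is 33 per group, with 70 recruited in total to allow for dropout.
- *Primary outcome*: "The changes in the child’s behaviour and anxiety levels". Six measures follow: four wrist-band parameters (electrodermal activity, blood volume pulse, heart rate, skin temperature), MCDASf and FBRS.
- *Role of the participants and the general public in the study*: refers to the "primary outcome measure of our study on investigating the differences in the participants reported dental anxiety scale", which is anxiety alone.
- *The study's statistical analysis*: two-group comparisons use a t-test or Mann–Whitney, and a p-"value of <0.05 will be considered significant in all tests".
- *Abstract, Conclusions*: the trial will report whether prior acclimatisation "is effective, or not, in improving dental treatment behaviour".

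**The concern.** A power figure means something only for a stated outcome, a stated difference and a stated rule for success. Here one figure covers two constructs, with no word on whether one or both must differ. The article itself gives three accounts of what is primary.

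The cited basis is a second difficulty. As described, the source concerns N2O in children sedated with diazepam. In this trial every child has N2O at the treatment visit, and the arms differ only in whether the child had 15 minutes of N2O at the earlier visit. The size of an N2O effect says nothing direct about the added benefit of having tried N2O once before.

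What is at stake is how a non-significant result will be read. The abstract promises a yes-or-no answer, and the 80% invites readers to take a null result as evidence that the extra visit does not work. The visit costs each child an additional N2O exposure and contact time, so a wrong conclusion in either direction matters.

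**Working it through.** **Inputs from the article.** 33 per group, 80% power and 70 recruited (sample-size section); 1:1 allocation (*Study flow and layout*); p < 0.05, t-test or Mann–Whitney (statistical analysis section).

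**Assumed, because not stated.** Two-sided testing; a continuous measure, with SD meaning the SD of the variable analysed; correlation between the behaviour and anxiety test statistics from 0 to 0.9.

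**1. The plan's own figures.** The 33 cannot be reproduced forwards, because the article shows no effect size, SD or rates. The 70 can: 66 / 0.95 = 69.5, rounded up to 70, which fits about 5% dropout (4/70 = 5.7% at most).

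**2. Difference detectable with 33 per arm at 80% power, one measure.**
- Normal approximation: d = (1.960 + 0.842) × √(2/33) = 2.802 × 0.2462 = 0.69 SD.
- Exact (noncentral t, 64 df): 0.70 SD.
- Mann–Whitney, replacing 33 by 33 × efficiency: 0.72 SD at efficiency 0.955 (normal data) and 0.76 SD at 0.864 (the lower bound).
- One-sided t-test: 0.62 SD.

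**3. Power at smaller differences (t-test, two-sided 5%, noncentrality d × √(33/2)).**

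| Difference | Power |
|---|---|
| 0.70 SD | 80% |
| 0.60 SD | 67% |
| 0.50 SD | 52% |
| 0.40 SD | 36% |

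For orientation only: the article gives no SD for MCDASf. If it were 4 to 6 points, 0.70 SD would be 0.70 × 4 = 2.8 to 0.70 × 6 = 4.2 points on the 6–30 scale.

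**4. Two constructs.** Suppose each test has 80% power, and write Φ₂ for the bivariate normal distribution function.
- Both must be significant: Φ₂(0.842, 0.842; ρ) = 64.0% at ρ = 0, 66.6% at 0.3, 68.7% at 0.5, 71.3% at 0.7 and 75.0% at 0.9.
- Either one suffices, unadjusted: 1 − Φ₂(−0.842, −0.842; ρ) = 96% at ρ = 0 and 89% at 0.7. The type I error for two independent tests is then 1 − 0.95² = 9.8%.

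The single figure of 80% matches neither rule. It fits only a single primary measure.

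**5. Precision.** The 95% CI half-width is t(0.975, 64) × √(2/33) = 1.998 × 0.2462 = 0.49 SD. An observed difference of 0.3 SD, for example, would give an interval from 0.30 − 0.49 = −0.19 to 0.30 + 0.49 = 0.79 SD. That is non-significant, yet compatible with a difference larger than the 0.70 SD the trial can detect.

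**The case against.** The strongest reply is that nothing here refutes the 80%. With no effect size visible, the figure can be neither confirmed nor denied, and 33 per arm does give 80% if 0.70 SD was assumed. A journal article condenses the full protocol, so the missing effect size and SD may be there. That is right: their absence is not the finding, and a reader who infers that the power is not delivered goes further than the document allows. Nor are alpha and the test missing, since the statistical analysis section gives both.

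A reader might also infer that the true power is 64–71%. The article does not support that. It nowhere requires both constructs to be significant, and two of its sections name anxiety alone, for which joint power is irrelevant. If either construct sufficed, power would be above 80%.

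It can also be said that the earlier study may have supplied only a variance or a score distribution, and that the authors disclose that no similar study exists. Both are fair. But no other basis is offered, and disclosure does not make the comparison the same. Whatever the full protocol adds, inputs drawn from that study would still come from a different contrast.

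Finally, no passage says which difference matters clinically, so 0.5 or 0.6 SD is the reviewer's choice, and detection is slightly more likely than not at both. That limits the claim about moderate effects. It does not touch the contradiction over what the 80% refers to.

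**Conclusion.** The point holds as a stated figure on a mismatched basis. The 80% is tied to behaviour and anxiety together, conflicts with the anxiety-only primary in the same section, and rests on a study that by its description tests something else. It is unsupported, not disproved.

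On one measure, 33 evaluable children per arm give 80% power for about 0.70 SD, or about 0.72 SD or more with Mann–Whitney, and close to even odds at 0.5 SD. These figures assume two-sided 5% testing and a roughly continuous outcome. They are solved backwards from 33 and do not reveal what the biostatistician assumed. The joint figure of 64–71% is conditional on a both-must-succeed rule that the protocol does not state, on 80% power for each test, and on a correlation of 0 to 0.7.

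With a half-width near 0.49 SD, a non-significant result should not be reported as showing that acclimatisation is ineffective.

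**What to change.** - In the sample-size section, claim power for one named primary measure. MCDASf fits that section and the participant-involvement section. Suggested wording: 33 evaluable children per arm give 80% power at two-sided 5% to detect a difference of about 0.70 SD in MCDASf. Add the equivalent in points once an SD has been chosen and justified.
- Label 0.70 SD as the detectable difference, not as the effect assumed when the trial was sized.
- State that no power is claimed for FBRS or the wrist-band parameters, and bring the *Primary outcome* section into line.
- Do not present the diazepam study as the basis for the acclimatisation effect. If it supplied something else, such as a variance, say so.
- In the abstract's Conclusions, replace the yes-or-no wording with a commitment to report the between-group difference with its 95% CI.

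The cost is a less favourable stated figure. No extra patients are needed, and neither the design nor the tests change.
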